## Abstract

**Background:**

Spastic hemiplegia following ischemic strokes seriously impedes the recovery of motor function posing a vast rehabilitation challenge. As the uncertain effects of recommended conventional treatments such as botulinum toxin injections on active functional improvement and potential adverse effects cannot be bypassed, there is an increasing need in alternative, more effective and safer modalities. Acupoints-based transcutaneous electrical nerve stimulation (Acu-TENS) and transcranial direct current stimulation (tDCS) are effective non-invasive modalities for stroke rehabilitation, particularly showing anti-spastic effect and functional improvements as well. However, the optimal stimulation frequency of Acu-TENS and whether combination of Acu-TENS and tDCS exert synergistic effect remain to be investigated.

**Objective:**

To evaluate the effects of Acu-TENS combined with tDCS on spasticity and motor function in ischemic stroke patients with spastic hemiplegia and screen the optimal frequency of Acu-TENS.

**Methods:**

A total of 90 post-ischemic stroke patients with spastic hemiplegia will be intervened for 4 weeks and followed up for 4 weeks. They will be randomly assigned to three groups including two observation groups and a standard care control group in a 1:1:1 ratio. All patients will receive standard care and regular rehabilitation accordingly. In addition, the two observation groups will receive 12 sessions of Acu-TENS at 20 Hz or 100 Hz for 30 min combined with 1 mA tDCS for 20 min, three times a week, for 4 weeks. The primary outcome is the change in total modified Ashworth scale (MAS) score from baseline to week 4. Secondary outcomes include changes in surface electromyography (SEMG), Fugl-Meyer Motor Function Scale, Modified Barthel Index (MBI), and 10-meter walk test from baseline to week 4. MAS score will also be measured after 4 weeks of follow-up. Adverse events throughout the study will be recorded.

**Discussion:**

This trial will evaluate, for the first time, the therapeutic potentials and safety of Acu-TENS combined with tDCS on spasticity and motor function in stroke patients. It will provide evidence for frequency-dependent anti-spastic effect of Acu-TENS, and a reference for rated parameter setting of new mixed transcutaneous and transcranial stimulation system for stroke rehabilitation, thereby promoting proactive healthcare consequently.

**Trial registration::**

Chinese Clinical Trials Register ChiCTR2200067186.

## Introduction

Stroke has become the main cause of human death and the leading cause of disability worldwide (1, 2), and ischemic stroke patients account for about 70% of the total number of strokes (3, 4). Spastic hemiplegia is characterized by the coexistence of muscle spasms and muscle weakness in one limb, which is the main motor dysfunction after stroke, posing a huge challenge for clinical treatment and patient rehabilitation, with heavy economic burden on healthcare system (5). Significantly, the incidence rate of spastic hemiplegia after stroke can be as high as 39.5% (6). Furthermore, for stroke patients with moderate or severe motor deficits, the increased muscle tone is as high as 97%, significantly reducing the patient’s quality of life (7, 8). Medications such as oral anti-spastic drugs (9), intramuscular botulinum toxin injections (10), and surgery (11) are the most common options for spastic hemiplegia after stroke. Although the effects of muscle relaxants on reducing resistance to passive movement have been confirmed, their uncertain effects on active functional improvement cannot be bypassed (12). Moreover, surgical risks and underlying adverse effects of anti-spastic drugs such as muscle weakness, sensory impairment, drug addiction, and hepatotoxicity (13, 14) should be considered. Additionally, since the prevalence rates of stroke rise significantly with age and is usually associated with poorer results (15), population ageing in many countries, especially in China, might lead to a substantial increase in the elderly stoke patients with complex medical care needs, driving up disease and care burdens (16, 17). Therefore, patients and their families as well as doctors aspire to more effective and safer therapies that can promote functional rehabilitation for the patients.

Emerging data including systematic reviews (18–21) and recent clinical studies (22) have shown that acupuncture and its related therapies, plays an important role in treating the patients with spastic hemiplegia following ischemic stroke. Clinically, using of several acupoints in one treatment session always exert better effects compared with a single point (22) due to the synergistic effect of acupoint combination (23). Applying transcutaneous electrical nerve stimulation (TENS) to stimulate specific acupoints, is a non-invasive acupuncture related therapy known as acupoints-based TENS (Acu-TENS) or transcutaneous electrical acupoints stimulation (TEAS). It is believed that Acu-TENS can induce signal transmission or restore the energy balance of the human body similar to acupuncture (24).

As a widely used noninvasive brain stimulation technique in recent decades, transcranial direct current stimulation (tDCS) via delivering a slight electrical current between two electrodes placed on the scalp, shows potential therapeutic effects for various neurological diseases including post-stoke spasticity (25). Interestingly, in acupuncture, a new developed innovative modality named scalp acupuncture has gained increasing interest for rehabilitation in stroke survivors with satisfied effects (26). However, scalp acupuncture may cause some adverse reactions such as stabbing pain, mild fainting or scalp hematoma (27), which consequently decrease the treatment compliance of patients to a certain degree. Therefore, we hypothesized that applying acupoints-based TENS on limbs combined with tDCS on scalp may perform synergic effect, so as to ameliorate spasticity and improve motor recovery in ischemic stroke survivors with spastic hemiplegia.

Clinical experience indicates that identifying appropriate application sites and stimulation parameters are crucial to the efficacy of any modalities based on acupoints. Evidence of the positive effects of tDCS on post-stroke spasticity has been provided by several studies (28–30), with similar intervention paradigm to stimulate affected motor cortex with a current in 1 mA. Actually, the core stimulation site of scalp acupuncture for post-stroke hemiparesis, named Anterior Oblique Line of Vertex-Temporal, is almost the same location as the surface area of motor cortex on the scalp (31). However, in the studies applying TENS or TEAS to post-stroke spasticity, although the anti-spastic effects are all satisfied, there is a wide range of frequency from 2 to 100 Hz (32–36). Thus, the optimal stimulation frequency of Acu-TENS remains unclear and needs to be furtherly investigated.

Based on the above, the present study aimed to evaluate the therapeutic effects and safety of Acu-TENS combined with tDCS for post-ischemic stroke with spastic hemiplegia. Since 20 and 100 Hz of TENS were the most commonly used frequencies in the majority of corresponding studies (32, 37), we attempt to investigate the optimal frequency of transcutaneous electrical stimulation by comparing the different stimulation frequencies at 20 and 100 Hz of Acu-TENS. Furthermore, it will provide a basis for future clinical trials with larger sample size and a reference for the rated parameter setting of new mixed acupoints-based transcutaneous electrical stimulation devices.

## Design and methods

### Study design

This is a prospective, assessor-blinded, randomized, controlled pilot trial with three parallel groups. A total of 90 post-ischemic stroke patients meeting the inclusion criteria will be recruited and then randomly allocated into 3 groups of 30 patients each. All patients will receive 4 weeks of standard care, and the patients assigned to 2 observational groups will receive tDCS and Acu-TENS treatments during a 4-week period (tDCS at 1 mA, Acu-TENS at 20 or 100 Hz) additionally. The stimulation waveform, sites, and duration will be kept the same throughout the study. This study will be performed in conformity to the principles of the Declaration of Helsinki. The “Standard Protocol Items: Recommendations for Interventional Trials” (SPIRIT) will be followed in reporting this protocol and the checklist is provided in Supplementary Material. The study protocol outline is presented as a flow chart in Figure 1, while the study timeline is illustrated in Table 1.

**Figure 1 fig1:**
[figure not shown]
Flow chart of the trial. Acu-TENS, acupoints-based transcutaneous electrical nerve stimulation; tDCS, transcranial direct current stimulation.

**Table 1 tab1:** Time schedule of the trial process.

	**Baseline**		**Treatment**				**Follow-up**
		Week 0	Week 1	Week 2	Week 3	Week 4	Week 8
**Enrollment**							
Eligibility screen	**×**						
Informed consent	**×**						
Random allocation		**×**					
**Interventions**							
Acu-TENS-20 Hz + tDCS			**×**	**×**	**×**	**×**	
Acu-TENS-100 Hz + tDCS			**×**	**×**	**×**	**×**	
**Standard care control**			**×**	**×**	**×**	**×**	
**Evaluations**							
MAS		**×**	**×**	**×**	**×**	**×**	**×**
SEMG		**×**				**×**	
Fugl–Meyer motor function scale		**×**				**×**	
MBI		**×**				**×**	
10-meter walk test		**×**				**×**	
**Adverse events**			**×**	**×**	**×**	**×**	

The intervention will last for 12 sessions, three times a week for 4 weeks. MAS, modified Ashworth scale; SEMG, surface electromyography; MBI, Modified Barthel Index.

### Recruitment

Post-ischemic stroke patients with spastic hemiplegia will be recruited from hospitals in Beijing, China. Posters and flyers will be used to recruit patients. Study information such as the purpose of the study, intervention methods, process and possible adverse reactions will be introduced to the potential participants. Patients will be screened according to inclusion and exclusion criteria by trained researchers. Informed consent will be signed prior to enrollment by patients who meet the requirements.

### Participants

#### Inclusion criteria

Patients meet all of the following criteria will be considered as eligible participants.

Patients with ischemic stroke confirmed by CT or MRI, with first onset of stroke, and onset of stroke for more than 1 month.The clinical symptoms include unilateral limb paralysis and motor dysfunction of upper and lower limbs.The modified Ashworth scale (MAS) rating of grade I or above for the major involved joint of the limb.Able to walk independently for 10 meters without help.Aged ≥18- years, regardless of gender.Stable state, clear consciousness, and no hearing and comprehension disabilities to complete the questionnaires.Participate voluntarily and sign an informed consent form.

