### Randomization and blinding

Eligible participants will be randomly assigned to 3 groups in a ratio of 1:1:1 by an independent statistician using a randomization sequence generated with SPSS 25.0 and will be concealed from the investigators. The random number of patients meeting criteria will be telephoned by the unaffiliated investigator. Due to the characteristics of interventions, participants in the standard care control group will be aware of their allocation ineluctably.

An independent researcher will pre-set the frequency of the Acu-TENS and then cover the frequency display site to ensure the operators remain blinded to the allocation (different frequencies of Acu-TENS) throughout the study. To reduce the risk of bias, the evaluators and statisticians will be blinded to group allocation during outcome assessment and data analysis.

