### Outcome measurement

#### Primary outcome

The primary outcome will be the change from baseline in muscle tone assessed with MAS in elbow, wrist, knee, and ankle 4 weeks after baseline (the end of the intervention). The detailed scoring rules of MAS with 6-level (level 0, 1, 1+, 2, 3, 4) are consistent with previous study (41). In the analysis of MAS scores, a derived MAS score with a 6-point scale from 0 to 5 (level 0, 1 equivalent to 0 and 1 respectively, level 1+ transformed into 2, 2 into 3, 3 into 4, and 4 into 5) will be used for practicality. To ensure the objectivity and accuracy of the MAS assessment, the independent evaluator will be instructed via specific training to use a medium velocity of passive movements, lasting about 1 s (42). Subsequently, MAS will be measured for above mentioned four joints with different levels in each joint, and then the sum of MAS scores in four joints will be recorded as the total MAS score.

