### Statistical analysis

Statistical analyses will be performed by statisticians who are independent of the research team and have no knowledge of the study groupings or study settings. Statistical analyses will be performed using IBM SPSS Statistics 25.0 software and follow intention-to-treat (ITT) principles to ensure all subjects are included after randomization. Missing data will be handled by multiple imputations. Continuous variables that follow a normal distribution are presented as mean ± standard deviation, and those that do not follow a normal distribution are given as median and interquartile range. Comparisons within groups will be performed via paired t-tests, and difference among groups will be analyzed by the one-way ANOVA test. For measurements at different time points, differences were assessed using repeated-measures ANOVA followed by Bonferroni *post hoc* tests. The test level is 0.05, with *p* < 0.05 indicating a statistically significant difference.

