### Elucidation of optimal stimulation parameters for Acu-TENS is essential for its effectiveness

Notably, spasticity rarely tends to resolve on its own but progressively worsens over time (50). Spasticity can exacerbate muscle weakness, leading to severe dyskinesia and further exacerbation of daily activities (51). Therefore, adequate and effective control of post-stroke spasticity is the key to break this vicious cycle, thereby fully facilitating motor recovery (48). Compared to medications and surgery, Acu-TENS therapy is a non-pharmaceutical and non-invasive modality that is more acceptable to patients.

The frequency used in an electrical stimulation therapy always plays a crucial role for its therapeutic effect. The frequency of Acu-TENS is worthy of exploring and researching, since it is used in variety, ranging from 2 to 100 Hz. Two Meta-analysis studies have shown that the frequency of TENS for post-ischemic stroke with spastic hemiplegia is mostly at 100 Hz (32, 33). TENS at 20 Hz has also been used in some studies, with positive effects of improving electromyography, relieving spasticity, and increasing walking speed (37, 52, 53). A very few studies compared the anti-spastic effects of TENS or TEAS at different frequencies in stoke patients. Only one study (36) investigated the effects of both 2 and 100 Hz of TEAS on muscle spasticity following brain injury, the results suggested that both low and high frequencies had anti-spastic effects while 100 Hz was better. Taken together, in this study, we will compare the effects of Acu-TENS at 20 and 100 Hz in treating post-ischemic stroke with spastic hemiplegia to explore the optimal Acu-TENS stimulation frequency. The results of this study could provide a reference for setting optimal rated parameters of noninvasive acupoint-based transcutaneous stimulator, which can be manipulated by patients themselves. This modulation may be an alternative option for some chronic diseases such as post-stroke sequelae, thereby promoting proactive rehabilitation of the elderly.

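### Entry is open at any time beyond 1 month after stroke, but the stated between-group analysis does not adjust for time since onset, which costs precision and leaves chance imbalance uncorrected

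*Protocol article*

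**What the plan says.** Under Inclusion criteria, patients qualify "with first onset of stroke, and onset of stroke for more than 1 month". Neither the inclusion nor the exclusion list gives an upper limit. The nearest restriction is "Stable state, clear consciousness, and no hearing and comprehension disabilities to complete the questionnaires", which carries no time window; the 6-month limits under Exclusion criteria concern earlier treatments, not the age of the stroke.

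Under Randomization and blinding, patients are "randomly assigned to 3 groups in a ratio of 1:1:1 by an independent statistician using a randomization sequence generated with SPSS 25.0". No stratum, block or minimisation factor is named.

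Under Statistical analysis, "difference among groups will be analyzed by the one-way ANOVA test". For measurements at several time points, "differences were assessed using repeated-measures ANOVA followed by Bonferroni" post hoc tests. Neither method is given a covariate.

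The outcome is defined as follows: "The primary outcome will be the change from baseline in muscle tone assessed with MAS in elbow, wrist, knee, and ankle", at 4 weeks. The Discussion, in the part on stimulation parameters, states that "spasticity rarely tends to resolve on its own but progressively worsens over time".

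**The concern.** A patient a few weeks past the 1-month threshold and one many years after stroke can both enter. If the change in MAS over 4 weeks depends on time since onset, this is a known source of variation that the described allocation does not balance and the stated test does not remove. Taking change from baseline allows for the starting level of MAS, but not for a different rate of change at different stages.

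Two things are at stake. The variation stays in the error term and lowers power. And in a given realised allocation, a contrast between arms carries part of any difference in time since onset. This matters most where the planned difference is small. Choosing between 20 and 100 Hz is a stated objective, and two of the three planned gaps are 0.25 and 0.30. The same reasoning applies to Fugl-Meyer, MBI and the 10-meter walk test.

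**Working it through.** **Inputs from the article (Sample size calculation).** Planned falls in MAS 1, 0.75 and 0.45; SD 0.52; two-sided alpha 0.05; power 90%; 24 per group, 30 after 20% dropout. The pairwise gaps are 0.25, 0.30 and 0.55. The article does not say which fall belongs to which arm.

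**Assumptions (no figure in the article).** 30% or 50% of patients are early after stroke. Early and late patients differ by g = 0.25 to 0.50 MAS points in 4-week change, on the scale of the planning figures.

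**1. The plan's own figure.** For a one-way ANOVA with three groups, the noncentrality is n × Σ(mean − grand mean)² / SD². The sum of squares about 0.7333 is 0.1517, so at n = 24 it is 24 × 0.1517 / 0.2704 = 13.46. Power is 0.892 at n = 23 and 0.905 at n = 24, so the minimum is 24. Then 24 / 0.8 = 30. Both figures reproduce.

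**2. Chance of imbalance.** Divide 90 patients, K of them early, at random into three arms of 30. The probability of a, b and c early patients is C(30,a) C(30,b) C(30,c) / C(90,K), with a + b + c = K. A difference of 20 points is 6 patients in 30.

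| Early share | 20 vs 100 Hz differ by ≥20 points | Any of three pairs, ≥20 points | Any pair, ≥30 points |
|---|---|---|---|
| 30% (K = 27) | 12.3% | 26.3% | 4.2% |
| 50% (K = 45) | 15.7% | 32.5% | 7.1% |

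**3. Which early-late gap is compatible with SD 0.52.** The share of variance due to stage is g² p(1 − p) / 0.2704.
- g = 0.25: 0.0625 × 0.21 / 0.2704 = 5% (p = 0.3); 0.0625 × 0.25 / 0.2704 = 6% (p = 0.5).
- g = 0.50: 0.25 × 0.21 / 0.2704 = 19%; 0.25 × 0.25 / 0.2704 = 23%.
- g = 1.0: 0.21 / 0.2704 = 78%; 0.25 / 0.2704 = 92%. This is not credible, so the range stops at 0.50.

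**4. Shift in a contrast.** Imbalance × g = 0.20 × 0.25 = 0.05, up to 0.20 × 0.50 = 0.10. That is 20-40% of the 0.25 gap, and 9-18% of the 0.55 gap.

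**5. Type I error of the unadjusted ANOVA** (simulation, 40,000 trials for each g, 50% early, 30 per arm).

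| | g = 0.25 | g = 0.50 |
|---|---|---|
| Overall | 4.96% | 5.05% |
| Given some pair ≥20 points apart | 6.1% | 8.5% |
| Given some pair ≥30 points apart | 6.6% | 14% |

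**6. What adjustment buys.** Replace the SD by 0.52 × √(1 − R²) and take off one degree of freedom. At 24 per arm, power is 90.5% if the covariate explains nothing, 92% at R² = 0.05 and 96% at R² = 0.20. The number per group for 90% power is 23 at R² = 0.05, 22 at 0.10 and 18 at 0.25, against the planned 24.

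**The case against.** The strongest reply is that chance differences between randomised arms are exactly what the ANOVA error term and the 5% level allow for. That stands. A reader might infer from the open entry window that the comparison is biased or the test invalid, and the documents do not support this: the overall type I error stays at 5%, and an imbalance is as likely to hide an effect as to mimic one.

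A reader might also take the 26-33% probability as the risk to the frequency comparison. It is the chance that any of three pairs is imbalanced; for the 20 versus 100 Hz pair it is 12-16%. Nor is it established that the 0.25 gap is the frequency gap, since the means are not assigned to arms.

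The article's remark that spasticity worsens over time does not say that the 4-week rate of change differs by stage; it makes such a dependence plausible without giving its size. Entry also requires spasticity of at least grade I, independent walking over 10 meters and a stable state, which narrows the spread by stage without removing it. Broad entry is a legitimate choice in a pilot, and time since onset is one of several possible covariates.

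Finally, an article commonly leaves strata and block sizes to the full protocol. Silence on stratification is therefore weak evidence that there is none. The same reply does not cover the analysis: a one-way ANOVA is named, and it has no place for a covariate or a stratum. If the full protocol does stratify, the test as stated would ignore the strata.

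**Conclusion.** The point holds as one of precision and conditional error, and it rests on the stated unadjusted analysis rather than on the absence of strata. Under the assumed early share and early-late gap, an imbalance of 20 points between the two frequency arms has a probability of 12-16% and moves their contrast by 0.05-0.10. That is material against a planned gap of 0.25 or 0.30 and minor against 0.55. Both assumed ranges lie outside the article; if time since onset has no bearing on 4-week change, there is no shift and nothing to gain. The sample size is reproduced and need not change. What makes the change worthwhile is the small price: the timing of onset has to be established for every patient to apply the 1-month rule, and adjustment leaves power at 90.5% even if the covariate proves useless.

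**What to change.** Replace the one-way ANOVA on change with a prespecified ANCOVA for total MAS, Fugl-Meyer, MBI and the 10-meter walk test. Include treatment arm, log time since onset and the baseline value of the outcome. Report time since onset by arm with the baseline characteristics.

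If recruitment has not started and the full protocol does not already do so, also stratify the randomisation list by time since onset and include the stratum in the model. The article offers no basis for a particular cut point, so the sponsor should choose and justify one beforehand. If recruitment is under way, leave the list alone; the covariate gives most of the benefit.

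The cost is a revision of the analysis section, one or two degrees of freedom and, where it applies, one change to the list. Eligibility, sample size, visits and measurements are untouched.
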